### Patient and public involvement

This research was done without patient or public involvement in conceptualisation, design, implementation, analysis, manuscript development or dissemination.

### Primary outcomes

The primary outcomes to assess the effectiveness of ICDS-CAS compared with the standard ISSNIP and ICDS are:The proportion of pregnant women and mothers of children <12 months who received adequate number of home visits by AWWs in the past 3 months (adequate number will be the minimum number of visits a respondent must receive as per ICDS guidelines for the current life-stage/age. Additionally, we will use, as a supporting indicator, the number of visits as a continuous outcome indicator.^26^); andThe proportion of pregnant women and mothers of children <12 months who received appropriate extent or level of counselling from AWWs during their interactions (at home, at AWCs or in other settings) in the past 3 months (appropriate level of counselling will be a recall of at least half of the correct messages/counselling that a respondent should receive as per ICDS guidelines for the current life-stage/age. Additionally, we will use, as a supporting indicator, number of correct messages or services recalled by the respondent as a continuous outcome.^26^).

### Secondary outcomes

Several outputs and outcomes according to the logic model presented in figure 2 are secondary outcomes in this evaluation study as discussed before. These include outcomes related to supervisory and capacity building support to AWWs, infrastructure and supplies at AWC, AWW level outcomes (motivation, satisfaction, knowledge, time allocation for services and record keeping, time allocation for service delivery, number of beneficiaries served) and additional ICDS services that can be improved by ICDS-CAS but also critically dependent on other external factors (growth monitoring of children, provision of IFA and supplemental nutrition, immunisation tracking, referrals, etc). We will also measure higher order but distal or aspirational outcomes related to knowledge, practices, health and nutrition at the beneficiary level.

### Outcome measurements

All beneficiary-level and AWW-level outcomes will be measured through structured interviews, with verification of registers and documents wherever possible. The household instruments were developed using standard questions from the WHO and Demographic and Health Survey frameworks, and capture information about the demographic and socio-economic characteristics of the household, birth history and family planning, pregnancy care, awareness and utilisation of AWC services at different life-stages, IYCF practices, immunisation, knowledge of health and nutrition and child health and nutritional outcomes (child growth). The AWW instrument captures information about coverage of beneficiaries, service delivery, supervisory support, work incentives and motivation, training received, time allocation, knowledge, and infrastructure and supplies at the AWC. The interviews are administered in *Hindi* on an android tablet-based SurveyCTO^TM^ platform.

### Analysis plan

The effects of the ICDS-CAS intervention will be estimated as,

$$Y_{ij,\;t=1}=\;\beta_{0}+\;\beta_{1}\;.\;T_{j}+Pair\;ID_{K}+{\overset{-}{Y}}_{j,t=0}\;+\;\varepsilon ,$$

where

$Y_{ij,\;t=1}$ = an outcome of interest for beneficiary *i* in village *j* at endline (*t*=1);

$T_{j}$ = indicator variable which is 1 for intervention and 0 for comparison villages;

$Pair\;ID_{K}$ = fixed effects to account for *k* pairs of matched villages;

${\overset{-}{Y}}_{j,t=0}$ = average pre-intervention or baseline (t = 0) level of the outcome Y in the village;

*ε* = the error term of the model; and

*β*
_1_ = the effect of the intervention on outcome Y.

We will adjust for the pre-intervention average level of outcome in a village (${\overset{-}{Y}}_{j,t=0}$) to control for, *at least*, the measured or unmeasured *time invariant* village-level and higher-level confounders. To the extent that the endline questionnaires or sampling are different from those in the baseline, the construction of the outcome indicators in the baseline and endline may differ slightly, but such differences (if any) will not affect the interpretation of impact parameters estimated using the above model specification. Additionally, as a consistency check, we will estimate adjusted treatment effects that control for any observed imbalance in important baseline covariates. We may additionally control for covariates that can help increase the precision of impact estimates. We do not plan to correct the p-values for multiple comparisons because we only test a limited number of indicators for primary outcomes. However, for secondary outcomes, when multiple indicators related to a topic or theme are compared, we will adjust the p-values for multiple comparisons. We also plan to estimate the effects by adjusting for pairing only at the district level and not at the village-level if accounting for village matching results in substantial sample loss. All analyses will be done in STATA and replicated by two different analysts.

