### Sample design and power calculations

The initial sample size was determined as 400 villages in each arm with one AWW and, on average, three mother-child dyads in each village to measure a relative effect of 15% in a standardised counterfactual outcome [Normal(0,1)], with a significance level of 0.05, power of 80% and intra-cluster correlation (ICC) of 0.15. The actual baseline survey sample consisted of 852 villages to account for refusals and loss to follow-up.

After the baseline survey was conducted in June-August 2017, completely separate from our efforts to design the evaluation, the Indian government decided to include ICDS-CAS in the National Nutrition Mission. Consequently, the original evaluation objectives were revised to estimate the effects of ICDS-CAS separately for MP and Bihar to draw deeper insights into the heterogeneity of impacts. Therefore, the evaluation sample needed to be powered to detect smaller magnitudes of effects on a few process-related secondary outcomes. We plan to increase the sample power by following the same panel of villages but recruiting almost twice as many participants in each village – up to two AWWs and up to eight mother-child dyads. Assuming 200 pairs of villages and 1200 mothers per arm in each state, the sample will have 80% power at a significance level of 0.05 to detect an absolute difference of 5%–9%-points from the counterfactual levels between 10%–50% with ICC between 0.15–0.30. With 400 AWWs per arm in each state, the sample will have 80% power to detect effects of 8–12%-points for AWW level outcomes from the counterfactual levels of 10%–40% with ICC between 0.25–0.45.

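### The printed regression names no variance estimator; with village-pair fixed effects, both ordinary and village-clustered standard errors would be too small, so clustering on the pair should be stated

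*Protocol article*

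**What the plan says.** The Analysis plan states that effects will be estimated from a linear model for beneficiary i in village j at endline. Its terms are a treatment indicator indexed by village, fixed effects for the matched village pairs, the baseline village mean of the outcome, and a residual without index, defined as "the error term of the model". The section also settles multiplicity, the software, replication by two analysts, and a fallback that adjusts for district pairing if village pairing loses too much sample. Neither it nor any other section mentions cluster-robust errors, a village random effect or an analysis of village summaries. The overview of the identification strategy promises only adjustment for the paired design.

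The section on sample design does plan for clustering. The initial size was set "with a significance level of 0.05, power of 80% and intra-cluster correlation (ICC) of 0.15". The revised size reads "Assuming 200 pairs of villages and 1200 mothers per arm in each state", with 80% power "to detect an absolute difference of 5%–9%-points from the counterfactual levels between 10%–50% with ICC between 0.15–0.30". For workers it reads "With 400 AWWs per arm in each state", with ICCs of 0.25–0.45.

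**The concern.** Treatment varies only between villages, so the precision of its coefficient depends on the number of villages and on how alike women in one village are. Pair fixed effects remove what the two villages of a pair share. They do not remove the correlation among women within one village. A variance computed from the printed model with independent residuals would therefore be too small.

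An analyst who noticed this would probably cluster on village, the unit that carries both the treatment and the planned ICC. With two villages per pair and pair fixed effects, that also gives too small a variance. At stake are the p-values and confidence intervals of both primary outcomes, which are tested without multiplicity correction and are meant to inform national scale-up. Replication by two analysts is no safeguard if both apply the same estimator.

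**Working it through.** **1. Does the plan's own power statement contain village clustering?** Inputs are from the section on sample design; a two-sided test is assumed.

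- Mothers: m = 1200/200 = 6 per village. Design effect 1 + (m − 1)·ICC = 1 + 5(0.15) = 1.75, or 1 + 5(0.30) = 2.50. Effective n per arm: 1200/1.75 = 686, or 1200/2.50 = 480.
- 10% against 15% with 686 per arm: SE = √(2·0.125·0.875/686) = 0.0179, and 0.05/0.0179 = 2.80 = 1.96 + 0.84.
- 50% against 59% with 480 per arm: SE = √(2·0.545·0.455/480) = 0.0321, and 0.09/0.0321 = 2.80.
- Both ends of the stated 5–9 points reproduce. With ICC = 0 the range would be 3.7–5.7 points.
- Workers: m = 400/200 = 2, design effects 1.25–1.45, detectable difference 7.6–11.9 points against the stated 8–12.

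The planning therefore relies on village clustering.

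**2. Ordinary errors in the printed model.** Let ρ be the ICC and s the share of village variance common to a pair (assumed; the article gives none). Leave out the baseline mean for the moment and put b = mρ(1 − s). The true variance of the treatment coefficient is proportional to (1 − ρ) + b. The residual mean square estimates (1 − ρ) + b/(2m − 1). Hence

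ratio of variances q = [(1 − ρ) + b/(2m − 1)] / [(1 − ρ) + b], and true type I error = 2[1 − Φ(1.96√q)].

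Example, m = 6, ρ = 0.15, s = 0: b = 0.90, q = (0.85 + 0.082)/1.75 = 0.532, √q = 0.730, type I error 15.3%.

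| | ρ | s = 0 | s = 0.5 | s = 0.9 |
|---|---|---|---|---|
| Mothers, m = 6 | 0.15 | 15.3% | 10.5% | 6.1% |
| Mothers, m = 6 | 0.30 | 24.9% | 17.1% | 7.7% |
| Workers, m = 2 | 0.25 | 9.3% | 7.4% | 5.5% |
| Workers, m = 2 | 0.45 | 13.4% | 10.1% | 6.2% |

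**3. Village-clustered errors with pair fixed effects.** In a pair with equal village sizes, the demeaned treatment is +½ and −½, and the residuals of the two villages sum to S and −S. Each village score is then S/2. Clustering on the pair squares the sum, giving S². Clustering on village adds the squares, giving S²/4 + S²/4 = S²/2, which is exactly half. With village sizes 4 and 8 the fraction is (4² + 8²)/12² = 0.56, so still close to half.

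- Without small-sample correction: SE ratio 1/√2 = 0.707, type I error 2[1 − Φ(1.386)] = 16.6%.
- With the usual correction for mothers (2400 women, 400 villages, 202 parameters): factor (400/399)(2399/2198) = 1.094, SE ratio √(1.094/2) = 0.740, type I error 14.7%.
- With the same correction for workers (800 in all): factor (400/399)(799/598) = 1.339, SE ratio 0.818, type I error 10.9%.

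**4. Simulation of the full printed model under no effect.** 200 pairs, baseline mean from 4 women per village (the baseline sampling number), half of the remaining village variance persisting from baseline (assumed), s = 0 to 0.5, 2000 datasets per setting. Rejection at nominal 5%:

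| Errors | Mothers | Workers |
|---|---|---|
| Ordinary | 10–24% | 7–13% |
| Village-clustered | 14–18%, depending on the small-sample correction | 10–12% (with correction) |
| Pair-clustered | 4–6% | 5–6% |

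A binary outcome at 30% with ICC 0.15 and s = 0 gave 10%, 15% and 5% for mothers. With village sizes varying from 4 to 8, village clustering still rejected in about 13–16%. With no pair effects in the model, village clustering gave 4.4%, so the fault in step 3 is specific to the pair fixed-effects model.

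**The case against.** The strongest reply is that this is silence, not error. A regression equation defines the coefficient to be estimated; the variance estimator is often given separately, and the article says that it guides a final analysis plan, which is not shown. Authors who sized the study on ICCs of 0.15–0.45 should not be presumed to analyse as if the ICC were zero. Village clustering, for its part, appears nowhere in the text.

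Most of this stands. A reader might infer that the trial will ignore clustering and that its primary p-values are therefore anti-conservative. The document does not support that: it neither says that residuals are independent nor that ordinary errors will be used. A reader might also apply the ICC of 0.45 to 6–8 women per village; that value belongs to workers at two per village, and for mothers the upper end is 0.30. Nor is the halving under village clustering exact in practice, since up to eight dyads may be recruited and village sizes may differ.

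What does not stand is that the matter can safely be left open. The article already fixes the pair fixed effects, and that choice makes the customary default of clustering on village fail as well. An analyst who completes the plan in either of the two obvious ways gets wrong error bars.

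**Conclusion.** The point holds in conditional form. The article fixes a model with village-level treatment and village-pair fixed effects, sizes the trial on substantial village ICCs, and names no variance estimator. Under that model ordinary errors would give a type I error of about 10–24% for mothers and 7–13% for workers. Village-clustered errors would give about 14–18% for mothers and 10–12% for workers, and pair-clustered errors about 4–6%.

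The figures for ordinary errors depend on pairing absorbing no more than half of the village variance. At about 90% they fall to roughly 5–8%, but nothing in the article supports so high a share. The village-clustering result hardly depends on that share; it follows from the pair structure. All figures assume a two-sided test and the planned 200 pairs per state; the simulated ones also use the baseline assumptions above. Only village-level correlation is covered. The programme was assigned by district, and correlation at that level is a separate matter that pair clustering does not solve.

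**What to change.** Add to the Analysis plan: in the model with village-pair fixed effects, standard errors are clustered on the matched village pair, for beneficiary and worker outcomes alike; village-level clustering is not used with pair fixed effects; in the district-pairing fallback, standard errors are clustered on village. Analysing pair differences of village summaries is an acceptable alternative for the main model.

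The change costs a sentence and a software option. The sample size stays as it is, because the stated detectable differences already include the design effect. The downside is wider intervals. For mothers, in the simulated settings with s = 0 to 0.5, the ordinary SE was 0.61–0.83 of the true one, so intervals become about 1.2 to 1.6 times as wide (1/0.83 to 1/0.61). Against village-clustered errors the factor is about 1/0.74 = 1.35.

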**Table 1 T1:** Comparison of matching performance in reducing bias

	Madhya Pradesh			Bihar		
	Ujjain-Dewas	Barwani-Alirajpur	Katni-Jabalpur	Samastipur-Darbhanga	Lakhisarai- Muzaffarpur	Sitamarhi-Jamui
Standardised mean bias - before matching	16.6	27.5	40.3	27	35.4	40.8
Standardised mean bias - after matching	6.5	8	9.9	8.3	6.6	9.7
% reduction in mean bias	61%	71%	75%	69%	81%	76%
P-value of LR test - before matching	0.000	0.000	0.000	0.000	0.000	0.000
P-value of LR test - after matching	0.929	0.929	0.905	0.788	0.997	0.490
Mean difference in propensity score	0.002	0.072	0.131	0.004	0.046	0.181

LR, log reduction.

*Recruitment of Study Participants*: In the already conducted baseline survey, we randomly sampled one AWC if more than one AWC existed in a selected village. Using the list of beneficiaries available at the selected AWC as a sample frame, we randomly sampled four mother-child dyads after stratification by life-stages: (1) mother of child aged <3 months, (2) mother of child aged three to <6 months, (3) mother of child aged six to <12 months and (4) mother of child aged 12 to <24 months. Additionally, we randomly sampled up to five pregnant women or mothers with a child <3 months for more in-depth analysis of ICDS services during pregnancy and child birth. To measure AWC-level outcomes, we conduct a survey of the selected AWWs as well.

The endline will be a repeated cross-sectional sample where pregnant women and mothers with children <12 months will be recruited using the list of beneficiaries available at the AWC at that time. We do not plan to recruit children older than 12 months at the endline because the ICDS-CAS intervention would be active for <12 months and we can realistically measure the changes only among children who were born after the ICDS-CAS implementation started.

All survey participants are/will be recruited for the study after being administered informed consent as per the Institutional Review Board approved protocol. Additional assent is taken just before taking anthropometric measurements (height and weight) of the children.

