### Baseline balance

Online supplementary tables 2 and 3 present the baseline balance at AWC, household and individual beneficiary levels. The balance is assessed in terms of group mean difference after adjusting for the pairing of villages. As a robustness check, the group mean differences obtained by adjusting only for the district pairing (and not the village pairs) are also presented. Overall, practically perfect balance in terms of exogenous variables such as household or individual characteristics is achieved, but there are a few differences in the AWC and AWW level characteristics and service delivery. Almost all indicators related to home visits and growth monitoring were balanced as the magnitude of the group differences are of little practical significance, except for the growth monitoring related outcomes in Bihar. A few secondary outcomes were meaningfully different as well. However, such differences are expected when more than 100 covariates and outcome indicators are tested for balance. We also do not see a discernible pattern where control or intervention groups are consistently better or worse off than the other group. Considering the preponderance of a highly similar distribution of variables, we infer that the matching resulted in exchangeable or balanced groups, and any residual confounding at the community level can be removed by controlling for the baseline outcomes.

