## Discussion

The evaluation will provide evidence on whether and to what extent ICDS-CAS mHealth can improve health and nutrition service delivery beyond what is feasible with traditional non-technology-based approaches under ISSNIP. Additionally, the analysis of a range of lower order outputs and outcomes can help us identify the pathways through which ICDS-CAS has worked, or the critical failure points.

The study faces a few limitations in identifying unbiased estimates of the programme effects due to the nature of the intervention and constraints on the study design. First, confounding or selection bias cannot be theoretically ruled out in an observational study such as ours. While the matching procedure appears to be successful, it may not have removed all residual and unobserved confounding. Measurement biases including the Hawthorne effect^27^ are possible because the outcomes are measured through interview recalls and observations. The external validity of the findings can be questioned because the purposive sampling of states, pairing of districts and the PSM-based sampling of villages do not result in a statistically representative sample of entire ICDS-CAS programme area. Finally, as is the case with most large-scale programmes, ICDS-CAS implementation may be delayed and the planned follow-up period may not be adequate for the impacts to materialise.

While these limitations are common in observational studies, the study team has tried to minimise the risk to validity of the findings by reducing the observed pre-intervention imbalance using a large set of variables from Census 2011 for matching, controlling for at least the cluster level time-invariant confounders by using a repeated cross sectional design, measuring the primary outcomes at the beneficiary level (beneficiaries will be blinded to their intervention status in the study), measuring a large set of indicators as per the logic model to test whether ICDS-CAS is working through hypothesised pathways and delaying the endline survey as much as possible before the intervention is implemented in the control districts. The evaluation framework also includes other components which can assess the intervention using mixed-methods approaches, and can help build confidence in the study findings.

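### Adjusting for the baseline village mean only partly removes time-invariant confounding, although the article says it controls for at least all of it

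*Protocol article*

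**What the plan says.** The Analysis plan regresses the endline outcome on an intervention indicator, pair terms described as "fixed effects to account for" the matched villages, and the village's mean outcome at baseline. On the last term it says: "We will adjust for the pre-intervention average level of outcome in a village". The stated purpose is to control for at least the measured or unmeasured time-invariant "village-level and higher-level confounders". If the baseline indicator is built differently from the endline one, the plan holds that "such differences (if any) will not affect the interpretation of impact parameters estimated using the above model specification".

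Two later sections rely on the same property. Baseline balance concludes that "any residual confounding at the community level can be removed by controlling for the baseline outcomes". The Discussion lists as a safeguard "controlling for at least the cluster level time-invariant confounders by using a repeated cross sectional design".

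On the size of the baseline sample, Sample design and power calculations gives "one AWW and, on average, three mother-child dyads in each village" as the initial design. The paragraph on recruitment of participants describes the survey as conducted: "we randomly sampled four mother-child dyads after stratification by life-stages", plus up to five pregnant women or mothers of a child under 3 months. One of the four core strata (12 to under 24 months) is not recruited at endline. One Anganwadi worker (AWW) per village was interviewed at baseline.

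The article states no difference-in-differences model, village fixed-effect model or correction for measurement error. The planned consistency check adjusts for observed imbalance in covariates.

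**The concern.** Full control of time-invariant differences, including unmeasured ones, is a property of differencing or of village fixed effects. In those models the baseline level is subtracted one for one. Here the baseline mean enters with an estimated slope. A mean of a few respondents is a noisy measure of the village's true level, so the slope is attenuated below 1, and only that fraction of a pre-existing gap is subtracted. This holds even for a gap between districts that the whole baseline survey measures well, because the slope is learned from noisy differences between individual villages.

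Assignment was not randomised. A reader who takes the claim at face value will believe that any fixed advantage or disadvantage of the intervention areas has been removed from β1. In fact part of it may remain and be read as an effect of ICDS-CAS.

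**Working it through.** **1. Are the article's inputs usable?** The revised design has 1200 mothers in 200 villages per arm and state, so 6 per village, with ICC 0.15–0.30. The effective number per arm is 1200/(1 + 5 × ICC), which is 686 at ICC 0.15 and 480 at ICC 0.30. At 80% power and α = 0.05 (two-sided assumed), the detectable difference runs from 5.0 points (10% level, ICC 0.15) to 9.0 points (50% level, ICC 0.30). The article states 5–9 points, so its figure reproduces.

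**2. What the model subtracts.** With two villages per pair and pair fixed effects, the model is equivalent to regressing the within-pair endline difference on the within-pair baseline difference, with β1 as the intercept. Suppose the true effect is zero and a gap G is present in both rounds. Then

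- slope b ≈ λ × s, where λ is the reliability of the baseline mean and s the stability of village effects over time;
- β1 ≈ G − b × G = (1 − λs) × G.

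For m respondents per village, λ = m × ICC / (1 + (m − 1) × ICC). For example, m = 4 and ICC = 0.15 give 0.60/1.45 = 0.41.

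**3. Share of a persistent gap left in β1** (s = 1; pairing explains no between-village variance):

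| Baseline respondents per village | λ at ICC 0.15 | Left | λ at ICC 0.30 | Left |
|---|---|---|---|---|
| 3 (initial design) | 0.35 | 65% | 0.56 | 44% |
| 4 (core sample) | 0.41 | 59% | 0.63 | 37% |
| 8 (maximum in life-stages also sampled at endline) | 0.59 | 41% | 0.77 | 23% |
| 9 (maximum overall) | 0.61 | 39% | 0.79 | 21% |

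For AWW outcomes there is one baseline worker, so λ equals the ICC. At the article's 0.25–0.45, 75–55% is left.

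**4. What raises the share.**

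- *Pair effects that absorb between-village variance.* If they absorb half (an assumption), λ = 0.5 × ICC / (0.5 × ICC + (1 − ICC)/m). The share left is then 74% and 54% for m = 4, and 56% and 34% for m = 9 (ICC 0.15 and 0.30).
- *Drift in village effects.* With s = 0.8 (an assumption), m = 4 and ICC 0.15 leave 1 − 0.8 × 0.41 = 67%.
- *A baseline indicator built differently.* The free slope absorbs a mere change of scale. A weaker correlation with the endline indicator lowers the fraction of the gap that is removed.

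**5. Simulation check.** The planned model was simulated with 200 pairs, 6 endline respondents per village and zero true effect.

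- Continuous outcome, gap of 0.10 SD: the share left was 63% (m = 3, ICC 0.15), 58% (m = 4, ICC 0.15) and 23% (m = 9, ICC 0.30), against 65%, 59% and 21% from the formula.
- Binary outcome at 30%, assumed 5-point gap in both rounds: β1 averaged 3.1 points (m = 4, ICC 0.15) and 1.0 point (m = 9, ICC 0.30). Rejection rates were about 28% and 9% against a nominal 5%.
- Binary outcome at 30%, assumed 2-point gap: rejection rates were about 6–8%.

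**6. In points.** A 2-point gap leaves 2 × 0.21 = 0.4 to 2 × 0.65 = 1.3 points.

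**The case against.** Several counter-arguments carry weight.

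- **Identification rests first on matching.** The overview of the identification strategy assumes that all confounders are measured and balanced. District pairs share a boundary and an ICDS division, and villages are matched on Census variables. Baseline adjustment is a second layer. This stands, so it would be wrong to call it the whole strategy.
- **The size of the gap is not established.** Baseline balance reports almost all home-visit indicators as balanced to a degree of little practical importance, with no consistent pattern favouring one arm. The supplementary tables with the figures are not at hand. A reader might infer that a large false effect will be reported, but the article does not support that. The 5-point gap above is an assumption, and it equals the lower end of the detectable range.
- **The 65% figure is the unfavourable end.** It needs only three usable respondents per village. With eight or nine, 21–41% is left. How many of the up to five extra women were found is not stated.
- **Difference-in-differences is not automatically better.** It assumes parallel trends, which the simulation builds in, so it had to come out unbiased there. Where a baseline gap is only sampling noise or fades by itself, conditioning on the lagged outcome does well and differencing over-subtracts. This also stands, and it rules out using difference-in-differences as a gatekeeper.
- **Limits are disclosed.** The Discussion concedes that matching may leave unobserved confounding. It then offers the baseline adjustment as mitigation and does not withdraw the claim made for it. The covariate check cannot reach unmeasured fixed differences.
- **The equation prints no coefficient on the baseline mean, so it might be fixed at 1.** The pair term has none either, and the text speaks of adjusting and controlling. With a slope of 1, a differently built baseline indicator would plainly matter, contrary to what the plan says.

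**Conclusion.** The claim of control over at least all time-invariant confounding is wrong as written in three sections. At the article's own ICC and baseline counts, the adjustment removes about 35–79% of a persistent gap and leaves about 21–65%. The share left is larger if pair effects absorb between-village variance, village effects drift, or the indicators differ between rounds.

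The shares assume that the planning ICC applies to the baseline data, that the gap is persistent and common to the pairs, and that village effects are stable. They do not apply to a gap that is only baseline sampling error.

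The absolute bias cannot be fixed from the article. It is probably small for home visits. It is unknown for counselling, the other primary outcome, which the balance statement does not name. It matters most for outcomes reported as imbalanced, such as growth monitoring in Bihar and a few secondary outcomes. The finding is that a stated safeguard is weaker than claimed, not that the primary result will be materially biased.

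**What to change.** 1. In the Analysis plan, Baseline balance and Discussion, replace the statements of full control or removal with wording that the model *partly adjusts for* time-invariant confounding.
2. Drop the statement that differently built baseline indicators leave the interpretation unaffected.
3. Keep the planned model as primary. For both primary outcomes, and for outcomes imbalanced at baseline, pre-specify a difference-in-differences sensitivity analysis with village fixed effects, round, and arm × round. Restrict it to life-stages sampled in both rounds (pregnancy and children under 12 months) and to identically built indicators.
4. Report both estimates with their assumptions: parallel trends for one, conditioning on the lagged outcome for the other. Discuss material disagreement as possible residual confounding. Do not require the two to agree before an effect is claimed.

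The cost is a change of wording and one extra regression per outcome, on data already collected or planned. In simulation with stable village effects, the standard error of the sensitivity estimate was about 5–31% larger than that of the planned model.
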